### Procedure

#### Study 1

All eligible patients will be offered participation in Study 1 and will be invited to complete the questionnaire (exclusion criteria: language other than Swedish, admission for <24 hours, severely ill, age <12 years old). We expect about 190 of the 350 patients admitted per year to be eligible for inclusion. The feasibility study indicated little attrition, but we anticipate that about 30% might not want to participate, leaving us with about 130 per year for possible inclusion.

**Figure 1 figure1:**
[figure not shown]
Study design with 3 randomization groups for the follow-up study at the Child and Adolescent Psychiatric Emergency unit, Malmö, Sweden. ICD-10: International Classification of Diseases, 10th revision; MADRS-S: Montgomery-Åsberg Depression Scale.

Patients and parents will be asked to complete questionnaires on psychiatric symptoms, treatment satisfaction, and quality of life. Included patients will be registered on The Blue App, allowing them to log in via their smartphone using a personal identity number at the log-in page (Figure 2).

The patients will then receive a short message service text message with a one-time password, enabling them to enter The Blue App and answer the questionnaires. It is also possible to generate one-time passwords and complete the questionnaires via The Blue App staff administration view. Parents can use their child’s log-in when answering the parental questionnaires.

The screening process at the unit will be divided into 3 stages (Figure 3). The first stage is defined as the first 24 hours at the unit. The second stage, during treatment, is defined as the time between intake and discharge. The discharge stage is defined as the last 24 hours at the unit. Patients and their parents will be given access to the questionnaires at each stage, which they will complete with the help of staff. At the unit, the questionnaires will be administered mainly on tablets, but can also be filled in via the patients’ own devices.

#### Study 2

At discharge, participation in study 2 will be offered to all patients who complete the questionnaires for Study 1 (Figure 3).

All patients in the study will receive treatment as usual at their outpatient units. Patients will use the same log-in procedure as in Study 1. With app-assisted technology, a link to the MADRS-S questionnaire (Figure 4) will be sent to all participants at predefined intervals depending on randomization.

**Figure 2 figure2:**
[figure not shown]
Screenshot of The Blue App login screen. Source: Region Skåne.

**Figure 3 figure3:**
[figure not shown]
Questionnaires used at the different stages during the inpatient stay at the Child and Adolescent Psychiatric Emergency Unit, Malmö, Sweden. ASSQ: Autism Spectrum Screening Questionnaire; AUDIT-C: Alcohol Use Disorders Identification Test-Consumption; DSHI-9: Deliberate Self-Harm Inventory-9; DUDIT: Drug Use Disorders Identification Test; HSCL-10: Hopkins Symptom Checklist-10; MADRS-S: Montgomery-Åsberg Depression Scale; MINI-KID: Mini International Neuropsychiatric Interview for Children and Adolescents; SDS: Sheehan Disability Scale; SNAP-IV: Swanson Nolan and Pelham Questionnaire; TSS-2: Treatment Satisfaction Scale 2.

**Figure 4 figure4:**
[figure not shown]
Screenshot of the MADRS-S (Montgomery-Åsberg Depression Scale) questionnaire item 7. Source: Region Skåne.

After discharge, researchers and staff will not be able to trace the group to which a patient is assigned. Patients readmitted to the ward during follow-up will remain in the study.

In group 1, feedback on depressive symptoms will be presented in a graph, together with a brief recommendation [31] on each follow-up occasion (Figure 5). A text below the graph will describe how patients can contact the emergency unit if they experience very severe symptoms or danger, with a button to make a direct call to the 24/7 emergency facilities.

**Figure 5 figure5:**
[figure not shown]
Screenshot of the MADRS-S (Montgomery-Åsberg Depression Scale) feedback screen for group 1. Source: Region Skåne.

Dropout analysis will examine for any group differences in terms of gender, age, and main International Classification of Diseases, 10th revision diagnoses. Information regarding reasons for missed appointments and dropouts will be taken from the medical records. Outcome measures are changes in MADRS-S scores and treatment compliance, as measured by attended outpatient appointments during the study period.

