### Design

#### Study 1

In Study 1, we want to map the prevalence of psychiatric comorbidity found in the medical records before and after the introduction of The Blue App. The hypothesis is that more diagnoses will be found in the records after the introduction of The Blue App.

#### Study 2

At discharge, eligible patients will be offered participation in a 1-year follow-up study using a randomized controlled design (Figure 1). After receiving informed consent, patients will be randomized into 3 groups and asked to answer questions regarding depressive symptoms (MADRS-S) at different time intervals over a period of 1 year after discharge. The time intervals were chosen to minimize dropout while being long enough to detect effects in the patient. We undertook a power calculation, as we found no comparable studies. Based on estimated scores on the depression rating scale (MADRS-S) at discharge, we expect scores at discharge to be around 30, with SD 7.1.

The null hypothesis for Study 2 is that no significant difference is found in the randomized controlled trial; that is, the feedback given through The Blue App would not improve the outcome or compliance. In the alternative hypothesis, we expect all patients to reduce their MARS-S scores during the study period and expect a difference of about 4 points on MADRS-S between intervention and control groups. With a power of .8, we will therefore need 3 groups of 50 patients each in order to detect differences at a 5% level.

#### Setting and Participants: Studies 1 and 2

Scania in southern Sweden has a population of over 1 million, of which 280,000 are children and adolescents. The university hospital in Malmö, the major city in the area, provides the only psychiatric emergency unit for children and adolescents, with 11 hospital beds. The hospital admits 350 unique patients annually together with a parent for acute stabilization. The most common reasons for admission are suicidal ideations, severely depressed moods, and acute crises. A majority of the patients are aged 13-17 years, with an even gender distribution.

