### Statistical Analysis

The two studies will be analyzed separately, and baseline variables will be analyzed with descriptive statistics. Pearson’s chi-square tests will be used to determine differences between the groups in terms of gender distribution and proportion of participants scoring above cut-off in the questionnaires used.

In Study 1, we will use descriptive statistics (mean, SD, median, interquartile range, continued variables, frequency and counts, categorical variations, and exact CIs for proportions) to describe the cohort and analyze differences in the number of psychiatric diagnoses before and after the introduction (*t* test) of The Blue App [32].

In Study 2, we will analyze differences between the 3 groups in terms of changes in MADRS-S scores and treatment compliance. Outcome measures (MADRS-S scores and dropout from outpatient care) will be analyzed according to intention to treat. Linear mixed model analyses will be used to identify changes over time in depressive symptoms and to examine compliance with outpatient treatments. In these analyses, group, time, and the intercept between the groups and time will be used as fixed effects and subjects as random intercepts.

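### The Study 2 MADRS-S model conditions on none of the variables chosen for the dropout analysis, so the group comparison can be biased if one of them predicts the MADRS-S course and relates to dropout differently by arm

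*Protocol article*

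**What the plan says.** The dropout plan is in Methods, Procedure, Study 2, in the text after Figure 5: "Dropout analysis will examine for any group differences in terms of gender, age, and main International Classification of Diseases, 10th revision diagnoses". The next sentence adds: "Information regarding reasons for missed appointments and dropouts will be taken from the medical records". No action is attached to what the dropout analysis finds.

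The outcome model is in Statistical Analysis: "Linear mixed model analyses will be used to identify changes over time in depressive symptoms", with terms given as follows: "In these analyses, group, time, and the intercept between the groups and time will be used as fixed effects and subjects as random intercepts". The word intercept before the groups and time is evidently a slip for interaction, and I read it so. The analysis principle is: "Outcome measures (MADRS-S scores and dropout from outpatient care) will be analyzed according to intention to treat".

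The planning figures are in Design, Study 2: "we expect scores at discharge to be around 30, with SD 7.1" and "expect a difference of about 4 points on MADRS-S between intervention and control groups", with 50 patients in each of three groups, power 0.8 and a 5% level.

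**The concern.** A likelihood-based mixed model uses every observed score. It handles dropout properly when the chance of a score being missing depends only on what the model conditions on, here arm, time and the patient's own observed scores. Gender, age and main diagnosis are outside that set, yet they are the variables the authors single out for the dropout analysis.

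The pattern to worry about depends on both arm and type of patient. It is plausible here. MADRS-S is collected over a year through links sent to the patient, and group 1 is described as receiving a graph and a recommendation on each occasion. Feedback might hold some kinds of patient and lose others. If those patients also recover at a different pace, their loss shifts one arm's estimated course relative to another's. The dropout analysis could reveal this, but nothing in the article carries the finding into the estimate reported as intention to treat.

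**Working it through.** **1. The plan's own figure.** With difference 4, SD 7.1, two-sided 5% and power 0.8, n per group = 2 × (1.96 + 0.84)² × 7.1² / 4² = 2 × 7.85 × 50.41 / 16 ≈ 49.5, so 50. Power at 50 per group is 0.804. The stated size reproduces. It does not bear on the bias question, but it supplies the 4-point yardstick.

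**2. Inputs that must be assumed.** The article gives no dropout rate and no covariate effects, and the visit schedule is in a figure that is not shown. Assumed: a binary covariate at 50% prevalence; 30% dropout overall; recovery differing by 4 or 6 points between covariate levels by the last visit; five visits; SD 7.1; within-patient correlation 0.5; 60% of dropouts leaving straight after discharge.

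**3. Hand approximation.** If dropouts contribute little follow-up, the spurious difference is roughly (difference between arms in the share of retained patients at level 1) × (difference in recovery). For mirror-image dropout of 10%/50% in one arm and 50%/10% in the other, the shares are 50/140 = 0.357 and 90/140 = 0.643. The difference is 0.286, giving 0.286 × 4 = 1.14 and 0.286 × 6 = 1.71 points.

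**4. Comparison with simulation.** The last column is a large simulation (200,000 patients per arm) of the model as listed, with time in categories.

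| Dropout by covariate level, arm A vs arm B | Share difference | Hand value, 4 / 6 points | Simulated bias, 4 / 6 points |
|---|---|---|---|
| Same pattern in both | 0 | 0 / 0 | about 0 |
| 30/30 vs 20/40 | 0.071 | 0.29 / 0.43 | 0.26 / 0.44 |
| 30/30 vs 10/50 | 0.143 | 0.57 / 0.86 | 0.59 / 0.78 |
| 40/20 vs 20/40 | 0.143 | 0.57 / 0.86 | 0.51 / 0.79 |
| 50/10 vs 10/50 | 0.286 | 1.14 / 1.71 | 1.13 / 1.65 |

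A simulation at trial size (50 vs 50, 400 trials per scenario, Monte Carlo error about 0.08) gave 0.2–0.4, 0.5–0.8, 0.4–0.7 and 1.1–1.6 for the last four rows. With three arms of 50, the mild pattern (20/40 vs 30/30) gave 0.25–0.4 and the mirror image 1.0–1.6.

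**5. When the bias vanishes or shrinks.** In a separate large simulation (200,000 patients in two arms, true effect zero, dropout times spread evenly over follow-up), mirror-image dropout gave:
- about 0.0 when the covariate was unrelated to MADRS-S;
- 0.31 when the covariate only shifted the level by 4 points (completers alone: 1.12), because dropouts' observed scores absorb most of the shift;
- 0.94 when it changed the course by 4 points;
- 1.23 when it did both.

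**6. Effect of adjustment.** Adding the covariate and its interaction with time brought the bias to within 0.1 point, that is, within simulation error, in every scenario.

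**7. Cost in precision.** One irrelevant binary covariate with its time interaction raised the standard error from 1.62 to 1.63–1.69. The full set (gender, age, four diagnosis groups, each by time) raised it from 1.62 to 1.66, and 1.66 / 1.62 = 1.025.

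**The case against.** **The article is condensed.** Covariate adjustment and missing-data sensitivity analyses are commonly left to an analysis plan that is not shown, so their absence alone is no error. That stands. What remains is narrower: the article does state which terms are the fixed effects, and it separately names the dropout variables. The point proposes a concrete change to a stated model.

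**A reader might infer that any dropout related to gender, age or diagnosis biases the result.** The documents do not support that. Two conditions are needed together: the variable must predict the unseen scores beyond those observed, and its link to dropout must differ by arm. Without either one, the simulated bias is about zero.

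**A reader might also take the upper figures as a forecast.** They are not. A recovery gap of 4 to 6 points between covariate levels is as large as or larger than the planned effect. Early departure of most dropouts leaves the model little to work with, and the mirror-image pattern is extreme. A mild bias of 0.2 to 0.4 points is small beside a standard error of 1.62.

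**The dropout sentence is ambiguous.** It sits beside missed appointments and medical records, and Statistical Analysis speaks of leaving outpatient care, so it may not concern unanswered questionnaires. Group differences could also mean dropouts against completers. Both ambiguities stand and need settling, but under either reading the variables are outside the listed model.

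**The remedy may be heavy.** With five visits and four diagnosis groups it adds 5 main effects and 5 × 4 = 20 interaction terms, 25 parameters in all. The full set was checked, and the loss of precision is small.

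**Conclusion.** The point holds in conditional form. The MADRS-S model as listed is protected only against missingness that depends on arm and observed scores, and it leaves out the variables the authors themselves chose for the dropout analysis. Bias in the group comparison is possible, not established.

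Under the assumed inputs, mild patterns give about 0.2 to 0.4 points, or 0.2/4 = 5% to 0.4/4 = 10% of the planned difference. Values over 1 point arise only with mirror-image dropout, and the bias is nil when all arms share the same pattern. The direction could favour or mask the intervention. The actual size cannot be derived from the article. This is an inexpensive improvement, not a demonstrated flaw in the result.

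**What to change.** In Statistical Analysis, add gender, age and main ICD-10 diagnosis to the fixed effects of the MADRS-S model, each with its interaction with time, whatever the dropout analysis later shows. Fix the diagnosis grouping (a few broad categories) before unblinding. Report the model with and without these terms, and correct intercept to interaction in the same sentence.

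In the Study 2 procedure, say that dropout includes missing MADRS-S responses and that group means randomised arm.

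The cost is a few sentences. The variables are already needed for the dropout analysis. If they prove irrelevant, the standard error rises by about 2 to 4%. The one new task is agreeing the diagnosis grouping in advance. Fixing the terms beforehand also avoids choosing covariates after the dropout pattern is known.

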### Ethical Approval

No compensation will be offered. Subjects in the study will be protected by the informed consent process. The Regional Ethical Board in Lund has approved the study (2013-06-19; Nr 423/2013).

### Statistical Analysis

The two studies will be analyzed separately, and baseline variables will be analyzed with descriptive statistics. Pearson’s chi-square tests will be used to determine differences between the groups in terms of gender distribution and proportion of participants scoring above cut-off in the questionnaires used.

In Study 1, we will use descriptive statistics (mean, SD, median, interquartile range, continued variables, frequency and counts, categorical variations, and exact CIs for proportions) to describe the cohort and analyze differences in the number of psychiatric diagnoses before and after the introduction (*t* test) of The Blue App [32].

In Study 2, we will analyze differences between the 3 groups in terms of changes in MADRS-S scores and treatment compliance. Outcome measures (MADRS-S scores and dropout from outpatient care) will be analyzed according to intention to treat. Linear mixed model analyses will be used to identify changes over time in depressive symptoms and to examine compliance with outpatient treatments. In these analyses, group, time, and the intercept between the groups and time will be used as fixed effects and subjects as random intercepts.

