**Methods:**

Two studies will be performed. Study 1 has a descriptive design, mapping comorbidities before and after the introduction of The Blue App. Study 2 has a randomized controlled design, measuring compliance with outpatient treatments as well as depressive symptoms, rated as changes in Montgomery-Åsberg Depression Scale scores during a 1-year follow-up.

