#### Step 6. Workshop With Adolescents: What Do the Patients Think?

During the development of The Blue App, feedback was obtained through a workshop with adolescent end users. The main aim was to assess the user-friendliness of the app. We arranged the workshop in spring 2016, during which 10 adolescents, 5 boys and 5 girls aged 14-17 years, participated. Of these, 2 adolescents were undergoing psychiatric outpatient treatment. The participating adolescents were introduced to the app and then navigated through The Blue App follow-up user interface. The participants found the app easy to navigate and suggested some minor improvements, such as the integration of graphic design.

### Planned Research Studies to Evaluate The Blue App: Research Studies 1 and 2

The objective was to design several studies to evaluate The Blue App. In the first study (Study 1), we aim to assess whether additional comorbid conditions could be identified using The Blue App. In the second study (Study 2), we want to evaluate whether the use of The Blue App can improve outpatient compliance and treatment outcome through feedback of psychiatric symptoms.

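### Study 1 tests recorded diagnoses before and after the app with a plain t test, which cannot separate the app from differences in case mix or recording practice

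*Protocol article*

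**What the plan says.** The article describes the purpose of Study 1 in three ways.

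- The abstract presents it as descriptive: "Study 1 has a descriptive design, mapping comorbidities before and after the introduction of The Blue App".
- The section introducing the two planned studies gives an evaluative aim: "we aim to assess whether additional comorbid conditions could be identified using The Blue App".
- The Design section says that the team wants to "map the prevalence of psychiatric comorbidity found in the medical records before and after the introduction of The Blue App", and adds a directional hypothesis: "The hypothesis is that more diagnoses will be found in the records after the introduction of The Blue App".

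For the analysis, the Statistical Analysis section lists descriptive statistics and states that they will be used to describe the cohort and to "analyze differences in the number of psychiatric diagnoses before and after the introduction" of the app, with a t test named for that comparison. The other group comparison named there is for categorical variables: "Pearson’s chi-square tests will be used to determine differences between the groups in terms of gender distribution", and likewise for the proportions above questionnaire cut-offs.

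On who is studied, Setting and Participants says "The hospital admits 350 unique patients annually". The Procedure section for Study 1 excludes patients who do not speak Swedish, stays under 24 hours, the severely ill and children under 12. It expects about 190 eligible patients a year, about 30% refusal and about 130 included per year. Data collection began in autumn 2017. The article does not state the dates, size or selection rule of the before group.

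**The concern.** The outcome is what clinicians wrote in the records, so it depends on who was admitted and how diagnoses were recorded as well as on the app. A t test on counts attributes the whole mean difference to period. If the patients differ, or if recording was already becoming more thorough, that difference enters the estimate with nothing to set against it.

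The article itself gives reasons to take this seriously:

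- The team was discussing missed comorbidity at the unit around 2013.
- A 2014 pilot at the unit found on average five areas of possible psychiatric interest that had not been clearly addressed or recorded.
- The app was demonstrated to unit staff during its development.
- The introduction describes agreement between clinicians on diagnosis as weak.

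Awareness of under-recording therefore predates the 2017 start by several years. This is not evidence that drift occurred, only that it is plausible.

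At stake is how the main result of Study 1 is read. A significant t test, set beside an aim framed around what the app identifies, would naturally be taken as support for the app. The Limitations section discusses the Swedish context, language and the selection into Study 2, but not comparability of the two periods in Study 1.

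**Working it through.** **Inputs from the article**

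- Eligible patients: about 190 of 350 per year (Procedure, Study 1).
- Expected refusal: about 30% (same place).
- Expected inclusion: about 130 per year (same place).
- Between-period test of counts: t test (Statistical Analysis).
- Not given for Study 1: SD of the counts, size of the before group, significance level. The 5% level, power of 0.8, difference of 4 points and SD of 7.1 in the Design section belong to Study 2.

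**The article's own figure**

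190 × (1 − 0.30) = 133, which agrees with about 130. No stated figure is wrong.

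**Illustration: how often the test rejects when the app does nothing**

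Assumptions: n patients in each period, a two-sided 5% level, no app effect, and a mean count that differs between periods by d standard deviations for other reasons. By the normal approximation:

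z = d / √(2/n)

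P(p<0.05) = Φ(z − 1.96) + Φ(−z − 1.96)

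For n = 130, √(2/130) = 0.124. At d = 0.2, z = 0.2/0.124 = 1.61 and P = Φ(−0.35) = 0.364.

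| Drift d (SD) | n = 130 per period | n = 260 per period |
|---|---|---|
| 0 | 0.050 | 0.050 |
| 0.1 | 0.127 | 0.207 |
| 0.2 | 0.364 | 0.626 |
| 0.3 | 0.677 | 0.928 |
| 0.4 | 0.897 | 0.995 |

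A longer study makes this worse, because the bias stays the same while the standard error shrinks.

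**In diagnoses per patient**

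With an assumed SD of 1.0 to 1.5 and n = 130, a drift of 0.2 diagnoses is 0.20 to 0.13 SD and gives p<0.05 in 36% to 19% of studies. A drift of 0.3 diagnoses does so in 67% to 36%.

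**Case mix alone**

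Assume two types of patient with means of 1 and 2 diagnoses, a within-type SD of 1, and 130 per period. If the more comorbid type rises from 40% to 60% of the cohort, the mean moves from 1.4 to 1.6. The variance is 1 + 0.4 × 0.6 = 1.24 in both periods. Then z = 0.2 / √(2 × 1.24/130) = 1.45 and P = 0.305. A rise to 50% gives 0.112, and a rise to 70% gives 0.589.

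**What the other named analyses add**

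The chi-square tests may show that the groups differ in gender or in the share above a cut-off. They do not carry that information into the comparison of counts, so they are not an adjustment.

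**The case against.** The strongest reply is that Study 1 is labelled descriptive, that mapping prevalence before and after is a modest goal, and that the hypothesis is worded in terms of time, not cause. A reader might infer that the plan credits any change to the app. The documents do not support that: no such conclusion is written, and the nearest wording is the aim about identification using the app. What remains is that this aim, a directional hypothesis and a significance test together go beyond description.

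A second reply is that covariates are often left to a fuller protocol or analysis plan, which is not shown. That is fair, and that the comparison is unadjusted is inferred from the t test being the only between-period test of counts named. But the article does name the test, and a t test has no place for covariates.

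Third, the size of the error is assumed. Nothing in the article shows that drift of any magnitude occurred, and the 130 per year describes inclusion in the app period, not the before group. The probabilities show only what would happen if the periods differed. This objection stands.

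Fourth, one might infer that the before group is retrospective, so that an earlier year is freely available to subtract a pre-existing trend. The article states neither. Subtracting the earlier change would also be a redesign. With equal groups, the variance of (after − before) − (before − earlier) is 6s²/n against 2s²/n for the simple difference, so the interval widens by √3, about 1.7 times. It further assumes that one year's change would have continued.

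**Conclusion.** The point holds as a cheap improvement to the analysis, not as an error in a figure or a contradiction that invalidates the study. Followed as written, the t test cannot tell an effect of the app from a difference in case mix or recording practice, and the Limitations section does not say so. The size is illustrative only: about 36% of studies would be significant at a drift of 0.2 SD and about 68% at 0.3 SD, given 130 patients per period, a 5% level and no app effect. The conclusion rests on the t test being the only between-period test of counts named, and on the aim being read as evaluative. It does not depend on any particular drift having occurred.

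**What to change.** 1. Replace the t test with a regression of the number of recorded diagnoses on period: negative binomial, or Poisson with robust standard errors. Adjust for age, sex, calendar month and main reason for admission. Report the rate ratio for period with its confidence interval.
2. Apply the Study 1 exclusion criteria to the before cohort and state its dates. The two periods should cover the same months, so that month can be adjusted for. Refusal in the app period cannot be mirrored this way and should be acknowledged.
3. Report the result as a before-after association. Adjustment addresses measured case mix but not drift in recording, so add secular change to the Limitations section.
4. If records and ethical approval allow, compare an earlier pre-app year with the before period using the same model, as an optional sensitivity check. It should inform interpretation and not redefine the effect estimate.

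The cost is extraction of a few routine covariates, modest extra analysis and a more cautious conclusion. Age and gender are already to be used in the Study 2 dropout analysis. The optional earlier year would add record extraction and might need its own approval.

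### The MADRS-S model as listed does not adjust for the discharge score, which generally costs precision, and the 80% power rests on a discharge-score SD that need not be the SD of change

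*Protocol article*

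**What the plan says.** The Procedure section for Study 2 defines the outcomes: "Outcome measures are changes in MADRS-S scores and treatment compliance". The Statistical Analysis section repeats this for the three-arm comparison ("we will analyze differences between the 3 groups in terms of changes in MADRS-S scores and treatment compliance") and then lists the terms of the linear mixed model: "group, time, and the intercept between the groups and time will be used as fixed effects and subjects as random intercepts". I read the word intercept there as interaction. No baseline covariate appears among the fixed effects, and nothing sets the arms equal at discharge.

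The sample size is in the Design section for Study 2. The spread is that of the score at discharge: "we expect scores at discharge to be around 30, with SD 7.1". The target is given as "expect a difference of about 4 points on MADRS-S between intervention and control groups", without saying whether it is a difference in score or in change. The conclusion is "With a power of .8, we will therefore need 3 groups of 50 patients each in order to detect differences at a 5% level".

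**The concern.** The trial expects to hold a MADRS-S score at discharge. The power paragraph assumes its mean and SD, and the Figure 3 legend includes MADRS-S among the inpatient questionnaires. Yet the listed model does not use that score as a covariate.

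If discharge is one of the response times, a free group effect gives each arm its own discharge mean, although randomisation makes those means equal in expectation. The group-by-time contrast is then a plain difference in change scores, which carries the discharge noise of both arms.

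The same choice affects the sample size. The SD of a change score depends on how strongly discharge and follow-up scores correlate. Using the discharge-score SD in its place ties the stated power to one particular correlation, which the article does not give. What is at stake is precision, and whether 50 per arm delivers 80% power for the analysis as planned.

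**Working it through.** **Inputs from the article:** difference 4 points; SD 7.1 (discharge score); 5% level; power 0.80; 50 per arm.

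**Assumptions not in the article:** correlation r between discharge and follow-up, taken from 0.2 to 0.7; the same SD of 7.1 at follow-up; discharge included as a response time; one contrast between two arms at a single follow-up; two-sided test; no dropout.

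**Step 1. Reproduce the stated size.** n per arm = 2 × [7.1 × (1.960 + 0.842) / 4]² = 49.46, rounded up to 50. Power at 50 per arm is 0.804 by the normal approximation and 0.797 by the noncentral t. A one-sided test would need 39 per arm, and a Bonferroni correction for two or three comparisons 60 or 66. The stated figure is therefore one uncorrected two-sided comparison with no allowance for dropout, and with 7.1 as the SD of the analysed outcome.

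**Step 2. What the group-by-time contrast estimates.** With categorical time, the discharge difference between two arms is the group effect, and the follow-up difference is the group effect plus the interaction. The interaction is thus the difference in change.

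**Step 3. Variances, with equal SD σ = 7.1.**
- Change: 2σ²(1−r), so SD = 7.1 × √[2(1−r)], which is 7.1 only at r = 0.5.
- Baseline-adjusted: σ²(1−r²), so SD = 7.1 × √(1−r²), never above 7.1.
- Share of variance saved: 1 − (1−r²)/[2(1−r)] = 1 − (1+r)/2 = (1−r)/2.

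**Step 4. Results for 50 per arm and 4 points (noncentral t).**

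| r (assumed) | SD of change | Power, change | Adjusted SD | Power, adjusted | Variance saved |
|---|---|---|---|---|---|
| 0.2 | 8.98 | 0.60 | 6.96 | 0.81 | 40% |
| 0.3 | 8.40 | 0.65 | 6.77 | 0.83 | 35% |
| 0.5 | 7.10 | 0.80 | 6.15 | 0.90 | 25% |
| 0.7 | 5.50 | 0.95 | 5.07 | 0.97 | 15% |

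**Step 5. Does the saving depend on the model or on the equal-SD assumption?**
- A generalised least squares check of a random-intercept model with categorical time, comparing a free with a constrained discharge difference, gives the same savings for the last-visit contrast with 1, 3, 6 or 12 follow-ups.
- With linear time the saving is about 8% to 47% over the same values of r and visit numbers. Power also changes with the number of visits, so the Step 4 powers apply to the single contrast only.
- If discharge is not in the response, the unadjusted comparison is of follow-up scores, and adjustment saves r²: 4% at r = 0.2 to 49% at r = 0.7.
- With unequal SDs s0 (discharge) and s1 (follow-up), the variance saved is (s0 − r·s1)², which is zero at r = s0/s1. For an assumed s1 of 10, the saving at r = 0.2 is (7.1 − 2)² / (50.41 + 100 − 28.4) = 26.01/122.01 = 21%. At r = 0.5 it is 4.41/79.41 = 6%, and at r = 0.7 it is 0.01/51.01, about 0%. The adjusted SD, 10 × √(1−r²), is then 9.80, 8.66 and 7.14, so the ceiling of 7.1 no longer holds.

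**The case against.** The strongest reply is that nothing here is an error. A comparison of change, or a group-by-time test, is unbiased under randomisation, and the sample-size arithmetic is right for its inputs. A condensed article may also leave covariates to a fuller document. The first part stands: this is a point about efficiency and about an unstated assumption. The second part limits its weight but does not remove it, because the article does not leave the model open. It names the fixed effects, and the discharge score is not among them.

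A second reply is that the model can be read in more than one way. The article does not say that discharge is a response time, it refers both to scores and to changes, and the follow-up questionnaire "will be sent to all participants at predefined intervals depending on randomization", with the schedule figure not shown. That also stands. It changes the size of the loss from (1−r)/2 to r² if the response is post-discharge scores only, but omitting the baseline still costs precision at any positive correlation.

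A reader might infer three stronger claims, and the article supports none of them:
- **That the plan wastes a fixed 15% to 40% of the variance.** This range comes from an assumed r and equal SDs, and neither is given.
- **That change scores are less precise at every r below 1.** This fails when the SDs differ, since the saving vanishes at r = s0/s1.
- **That the trial is underpowered.** Under equal SDs, power is below 0.80 if r is under 0.5 and above it if r is over 0.5. A low correlation after an acute admission is plausible, but nothing in the article establishes it.

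**Conclusion.** The point holds in a conditional form. The listed MADRS-S model leaves out the discharge score, so it gives a valid comparison that is generally less precise than an adjusted one. The stated 80% power is not established for a change outcome and could be higher or lower: about 0.60 to 0.95 over r = 0.2 to 0.7 for the single contrast, against 0.81 to 0.97 with adjustment. These figures rest on equal SDs of 7.1, discharge as a response time, one two-sided comparison of 50 per arm and no dropout. Adjustment matters most where the change-score analysis is weakest: under equal SDs it keeps the outcome SD at or below 7.1, and so keeps power at about 0.80 or better before dropout whatever r is.

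**What to change.** Make two additions.

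1. In the Statistical Analysis section, state that the MADRS-S model adjusts for discharge MADRS-S. Either enter it as a covariate with post-discharge scores as the response, or keep discharge in the response and constrain the arm means to be equal there. Report the baseline-adjusted group difference at a named time. In the same sentence, change intercept to interaction.
2. In the power paragraph, state that the 80% assumes an SD of 7.1 for the analysed outcome, say whether the 4 points is a difference in score or in change, and note that baseline adjustment would not exceed that SD if the follow-up SD equals the discharge SD.

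The cost is two or three sentences. No extra patients or measurements are needed, because the discharge score is already anticipated.
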